**Research Protocol**

Synopsis

This pragmatic trial with cluster randomization of AEDs is designed to evaluate the effectiveness and cost-effectiveness of screening methods (modified PAT vs FAST vs modified SASQ) and interventions (Leaflet vs Brief advice vs Brief counselling) in routine AED care. Due to the design implications of a multi-level factorial design in AEDs the proposed trial involves a universal screening approach in which relevant data for a sub-sample of linked presentation population is collected. Therefore, the trial design encompasses a 3x3 factorial trial, screening method (modified PAT vs FAST vs modified SASQ) and intervention (Leaflet vs Brief advice vs Brief lifestyle counselling). The main advantages of utilising a factorial approach are twofold. First each of the three elements (screening tool and intervention) can be analysed independently with sufficient power to make meaningful interpretation of relative effectiveness. Second, the method enables meaningful interpretations of the relative effectiveness of any combination of screening method and intervention. Because the universal screening population encompasses a sub-group of linked presentation targeted population we can make meaningful comparisons of the relative effectiveness and interactions associated with screening approach in AEDs. Nine AEDs across the North East, London and the South East Regions of England will be recruited. AEDs will be randomly allocated to one of three intervention conditions: the patient information leaflet control condition (n=3), the structured brief advice condition (n=3); and lifestyle counselling by an Alcohol Health Worker (n=3). To test the relative effectiveness of different screening methods all AEDs will be randomised to either a modified single item screen (Single Alcohol Screening Question; M-SASQ) or a modified Paddington Alcohol Test (SIPS-PAT) or FAST Alcohol Screening Test (FAST) screening method. AEDs in the modified PAT condition will use targeted screening as per the standard PAT protocol. AEDs in the FAST and modified SASQ conditions will use universal screening for case identification and collect information about whether a patient would be part of a linked presentation group and then use statistical simulation to analyse any interactions. Screening randomisation will be stratified by median AED admission rates (2 levels) and intervention condition (3 levels). Each AED will recruit a minimum of 131 patients who are hazardous or harmful drinkers into the trial and a short baseline assessment will be carried out. Outcome will be assessed at 6, and 12 months after intervention. Outcomes will include system implementation outcomes and patient outcomes. We will also examine the practitioner and organisational factors associated with successful implementation.

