
Study aim

To evaluate the implementation, effectiveness and cost effectiveness of BI delivered by an alcohol health worker aimed at reducing excessive drinking in routine AED care compared to brief advice and a patient information leaflet (PIL) in hazardous and harmful drinkers identified by universal or targeted screening.

Study objectives

- To conduct a pragmatic multicentre cluster randomised controlled trial of screening and brief interventions for hazardous and harmful drinkers in AEDs in three English regions.
- To compare the effectiveness and cost effectiveness of brief advice conducted by AED staff (including dedicated AHWs) (Tier 1) with referral to an alcohol health worker (Tier 2) of patients with hazardous and harmful alcohol consumption identified by targeted opportunistic or universal screening.
- To assess the relative impact of the three implementation strategies on alcohol screening and brief intervention activity in AEDs.
- To identify the attitudinal, practical, skill, resource, and reinforcing factors that predict successful implementation of screening and brief intervention in AEDs.
- To identify the optimal method of alcohol screening in AED.
- To assess the relative impact of the three implementation strategies on uptake of alcohol services, including an alcohol helpline.

Hypotheses

- Brief Lifestyle Counselling intervention by an alcohol health worker for hazardous and harmful drinkers identified by targeted screening is more effective and cost effective than Brief Advice conducted by AED staff (including dedicated AHWs) in the typical AED setting.
- Brief Lifestyle Counselling intervention by and alcohol health worker and Brief Advice by AED staff (including dedicated AHWs) are more effective and cost effective than an information leaflet alone.
- Access to referral to an alcohol health worker results in greater screening and intervention activity than training of AED staff in screening and brief intervention alone.
- Attitudinal, practical, skill, resource, and reinforcing factors predict screening and intervention activity.
- Briefer screening methods result in greater implementation of screening activity than more complex methods.

Setting

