The research team will identify the total number of patients over 18 attending each AED during the recruitment period, the total number of patients screened, the number screening positive, and the number receiving an alcohol intervention (either a leaflet or brief advice by AED staff (including dedicated AHWs)or brief lifestyle counselling intervention by the AHW) according to the method described by Babor et al. (2005). This will allow calculation of the overall screening rate, the screen conversion rate (proportion of positive screens), and the intervention rate in the different settings. We will also compare these measures between AEDs assigned to the SIPS-PAT versus the modified SASQ versus FAST screening methods.

Reattendence to AEDs over the 6, and 12 month follow up period of patients participating in the study will be assessed using computerised admission records and compared with admissions by the participating group of patients in the 6 month before entry into the study. The sustainability of the screening and intervention approaches will be assessed by examining the extent to which screening and intervention activity continues after the end of the formal study recruitment period.

Patient measures:

*Baseline*

Before receiving the initial PIL and/or brief advice intervention and/or brief lifestyle counselling intervention, participants will be invited by AED staff (including dedicated AHWs) to provide the contact details and complete the Extended AUDIT, EQ5D, Short-SUQ and modified Readiness to change Ruler. Participants in the extended intervention will complete the AUDIT at the same stage as those in other groups.

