The sample size calculation is designed to account primarily for intervention level outcomes. Powering the study in this way will also account statistically for appropriate outcomes for screening approach and screening method. The primary outcome for this study is the proportion of patients who consume alcohol within recommended levels at 6 month follow up. Recent meta-analysis (Moyer et al 2002) suggest that the difference between brief intervention and control is of the order 13%, 5% reduction in the control group and 18% in the brief intervention group. In order to detect a difference of this magnitude at the 5% significance level with 80% power, for a 2-sided test, requires 109 patients in each of the 3 groups, a total of 327. Our experience with other multi-centre randomized controlled trials of interventions for alcohol use disorders suggests that with assiduous follow-up the potential loss to follow-up across groups is of the order 25%. Taking this loss into accounts inflates the sample required to 131 in each group, a total of 393 patients per intervention.

The proposed study involves a cluster design and requires a statistical adjustment to account for any potential cluster effect. The literature, and our previous experience of trials in primary care, suggest an intra-class correlation coefficient of 0.04 is appropriate. Assuming a cluster size of the order 131 patients this inflates the sample size calculation by a factor of 2.7 requiring patients 393 in each group, a total of 1179, with an expectation that at least 882 will be followed up at 6 months.

We propose to recruit 9 AED’s. AED populations will be screened using 1 of 3 screening method groups (3 AED’s in each group) and will receive 1 of 3 intervention (3 AED’s in each group).

Planned analysis

As the study is pragmatic in design, the planned analysis will be by intention to treat. The primary outcome is dichotomous in nature, drinking within or above recommended levels, and will be analysed logistic regression adjusting for all known prognostic factors, data will be presented as odds ratios and their corresponding confidence intervals. Secondary analyses will be undertaken using the appropriate method for the outcomes, controlling where appropriate for intake values and other known prognostic variables using analysis of covariance. Simulations will be undertaken to encompass both screening approach groups and intention to treat analysis will be undertaken on both groups.

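### The protocol says its patient-level sample size also covers screening method and screening approach, but no power has been shown for either

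*Protocol*

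**What the plan says.** The Protocol's section on sample size calculation rests on one contrast, brief intervention against control, for the proportion of patients drinking within recommended levels at 6 months. The assumed figures are "5% reduction in the control group and 18% in the brief intervention group". Detecting that difference "at the 5% significance level with 80% power, for a 2-sided test, requires 109 patients in each of the 3 groups". After allowances for loss to follow-up and clustering (ICC 0.04), the section arrives at 393 patients per intervention and 1179 in all.

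The same section says that the calculation is aimed mainly at the intervention outcomes, and then continues: "Powering the study in this way will also account statistically for appropriate outcomes for screening approach and screening method". The Synopsis says of the factorial design that "each of the three elements (screening tool and intervention) can be analysed independently with sufficient power to make meaningful interpretation of relative effectiveness".

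The screening outcomes are described elsewhere. The last hypothesis reads: "Briefer screening methods result in greater implementation of screening activity than more complex methods". The subsection on system measures defines an overall screening rate, a conversion rate and an intervention rate, and adds: "We will also compare these measures between AEDs assigned to the SIPS-PAT versus the modified SASQ versus FAST screening methods". The Design section and Table 1 give three AEDs per screening method. Targeted screening is used only in the three PAT AEDs and universal screening in the other six. The Design section also says that a separate universal v targeted factor would have needed at least 18 AEDs.

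**The concern.** The calculation concerns one patient-level outcome and one factor. The screening rates are properties of an AED, with attenders, screened patients or positive screens as denominators. Enrolling more screen-positive patients does nothing for their precision, which is governed by how much AEDs differ from one another and by having three of them per method. No effect size, base rate or between-AED variance is given for any screening outcome, so the statement that they are covered has nothing behind it.

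Finding the best screening method is a stated objective, and the comparison of targeted with universal screening is meant to feed clinical guidelines. A reader who takes the power statements at face value could treat a non-significant difference between tools as an adequately powered negative result.

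**Working it through.** **Step 1. The protocol's base figure.** Inputs: 5% v 18%, two-sided 5%, 80% power. The pooled two-proportion formula gives n = [1.96·√(2·0.115·0.885) + 0.842·√(0.05·0.95 + 0.18·0.82)]² / 0.13² = 93.3. With the continuity correction, n = (93.3/4)·[1 + √(1 + 4/(93.3·0.13))]² = 108.2, which rounds up to 109 as stated. The formula is therefore a patient-level comparison of two proportions, with no screening quantity in it.

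The later steps do not reproduce: 109/0.75 gives 146, not 131, and 1 + 130·0.04 gives a design effect of 6.2, not 2.7. Those are separate matters, and nothing below depends on them.

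**Step 2. Screening rates, with the AED as unit.** Assumptions, since the protocol supplies none for these rates: a difference of 13 points and an ICC of 0.04, both borrowed from the drinking calculation; ICCs of 0.01 and 0.10 as a range; base rates p from 10% to 50%. Within-AED sampling error is ignored, which favours the protocol.

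- Between-AED SD = √(ICC·p·(1−p)).
- SE = SD·√(1/k₁ + 1/k₂), where k₁ and k₂ are the numbers of AEDs compared.
- Power comes from the noncentral t at two-sided 5%. Residual df are 9−1−2−2 = 4 with both factors fitted. With screening alone fitted they are 9−1−2 = 6 for three methods, or 9−2 = 7 for two approaches.

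Worked case, p = 50% and ICC 0.04: SD = √(0.04·0.25) = 0.10. For three v three AEDs, SE = 0.10·√(2/3) = 0.0816 and the noncentrality is 0.13/0.0816 = 1.59. Power is 23% (4 df) or 27% (6 df).

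Three v three AEDs, over p = 10–50% and 4–6 df:

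| ICC | Power for 13 points | Difference detectable with 80% power |
| --- | --- | --- |
| 0.01 | 67–99% | 8–15 points |
| 0.04 | 23–60% | 17–31 points |
| 0.10 | 12–29% | 26–49 points |

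The detectable difference is 3.07 SDs with 4 df and 2.75 SDs with 6 df. At ICC 0.04 that runs from 2.75·0.06 = 16.5 points (p = 10%) to 3.07·0.10 = 30.7 points (p = 50%).

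Three PAT AEDs v six universal AEDs, 4–7 df, 13 points:

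- p = 50%, ICC 0.01: 78–88%.
- p = 10%, ICC 0.04: 64–75%.
- p = 50%, ICC 0.04: 29–36%.
- p = 50%, ICC 0.10: 15–17%.

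**Step 3. The other reading: 6-month drinking by screening method.** Table 1 puts 393 patients in each screening margin. With 25% loss, 393·0.75 ≈ 295 are followed up, or about 98.25 per AED. The design effect at ICC 0.04 is 1 + 97.25·0.04 = 4.89, and the effective n is 294.75/4.89 ≈ 60 per margin. Power for 5% v 18% is 61% by the normal approximation and 42% by t with 4 df. With three AEDs per margin the effective n cannot exceed 3/0.04 = 75, so power stops near 71% (normal) however many patients are enrolled.

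**The case against.** Four stronger readings are tempting, and the documents do not support them.

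- **That the screening comparisons have no power.** With no effect size, base rate or variance stated, power is undemonstrated, not absent. At ICC 0.01 it passes 80% in several of the cases above.
- **That the enrolled numbers are irrelevant to screening method altogether.** The claim in the sample size section refers only to suitable outcomes. The Synopsis lists patient outcomes as well as system outcomes, and each screening margin in Table 1 holds as many patients as each intervention margin. If 6-month drinking is meant, the 393 does enter. Power then falls short because there are three AEDs per margin, a weakness that the intervention contrast shares. The 13-point gap is also an intervention effect, and nothing ties it to the choice of screening tool.
- **That screening approach is studied only as three v six AEDs.** The Design section plans two routes. The second uses presenting conditions and demographics recorded in the universal-screening AEDs, and the Synopsis and planned analysis add simulation. The three v six figures do not describe that route.
- **That a null result will be read as no difference.** The protocol does not say so. The power statements invite that reading, and no more can be said.

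It is also fair that the sample size section calls the intervention its main target, and that the Synopsis credits the factorial design, not this calculation, for its power. Both remain positive statements about screening that no figure in the protocol supports.

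**Conclusion.** The point stands as a claim without support. The sample size section says that screening approach and method are accounted for, and the Synopsis says that each element has sufficient power, but the protocol shows power for neither factor. For AED-level rates the outcome depends on the ICC: a 13-point difference between two methods would be reasonably well covered at 0.01 and poorly covered at 0.04 or above. On the patient-outcome reading, power at the protocol's own ICC stays below 80%. The AED-level figures rest on an effect size, base rates and ICCs that the protocol does not give for screening. The lack of any supporting calculation does not rest on those assumptions. The intervention comparison and the primary outcome are not at issue here.

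**What to change.** - Delete the sentence in the sample size section that extends the calculation to screening approach and method. In the Synopsis, limit the power claim to what has been calculated.
- State that the comparison of screening methods (three AEDs each) and the randomised comparison of approaches (three PAT v six universal AEDs, inseparable from the tool) were not powered.
- Give the AED-level detectable difference over a range of ICCs and base rates, for example about 17–31 points between two methods at ICC 0.04 and rates of 10–50%.
- Keep the second route for screening approach, using recorded presentation in the six universal-screening AEDs with simulation, as a separate analysis with no stated power.
- Report the screening comparisons as estimates with confidence intervals that treat the AED as the unit, and say that a non-significant result is not evidence of no difference.

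The cost is rewording in two sections and a short table. No further AEDs or patients are needed. The stated precision for the screening questions will look less favourable.

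### The protocol claims sufficient power for relative effectiveness across the intervention factor, but sizes the trial only on brief intervention v control; counselling v brief advice has no planning effect and falls short of 80% power

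*Protocol*

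**What the plan says.** Protocol, Synopsis, on the advantages of the factorial design: "each of the three elements (screening tool and intervention) can be analysed independently with sufficient power to make meaningful interpretation of relative effectiveness". The intervention factor has three levels: leaflet, brief advice and brief lifestyle counselling.

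Protocol, Hypotheses, first item: counselling by an alcohol health worker "is more effective and cost effective than Brief Advice conducted by AED staff (including dedicated AHWs) in the typical AED setting". The item is restricted to drinkers found by targeted screening. The second item sets both active interventions against the leaflet. The second study objective also compares advice (Tier 1) with referral to the alcohol health worker (Tier 2), but for patients found by either targeted or universal screening.

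Protocol, Sample size calculation: "The sample size calculation is designed to account primarily for intervention level outcomes". It takes from a meta-analysis that "the difference between brief intervention and control is of the order 13" per cent. The only planning rates are "5% reduction in the control group and 18% in the brief intervention group". Tested "at the 5% significance level with 80% power, for a 2-sided test", this "requires 109 patients in each of the 3 groups, a total of 327". No rate or difference for counselling v advice appears anywhere in the protocol.

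Protocol, Brief intervention implementation conditions, item 3: counselling patients also receive the leaflet and the structured advice before they leave the department.

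**The concern.** The power claim is broader than the calculation behind it. A reader of the Synopsis will take relative effectiveness on a three-level factor to include counselling v advice. The calculation supports only a comparison with the leaflet.

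The two contrasts differ in two ways that lower power. First, counselling is given on top of the leaflet and structured advice, so the contrast measures an increment over an active intervention. Second, if advice works as the second hypothesis expects, the comparison starts from a rate above 5%, where the binomial variance is larger. The same 13-point difference is then harder to detect.

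At stake is how a null result is read. Services deciding whether to pay for alcohol health workers could take a non-significant difference as no added benefit, because the trial is described as sufficiently powered.

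**Working it through.** **Inputs from the protocol.** Rates 5% and 18%; two-sided 5% level; 80% power; 109 per group; 25% loss; stated inflation factor 2.7; 393 recruited per arm; 882 followed up in total (all from Sample size calculation). Three departments per intervention, 131 patients each (Table 1).

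**Reproducing the stated figure.** The two-proportion formula with pooled null variance is

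n = [1.96·√(2p̄(1−p̄)) + 0.842·√(p1(1−p1)+p2(1−p2))]² / (p2−p1)².

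For 5% v 18% it gives 94 per group. The continuity correction, n/4·[1+√(1+4/(n·|p2−p1|))]², raises this to 109, the protocol's figure. Then 109 × 2.7 / 0.75 = 392.4, which agrees with 393. The planned size therefore rests wholly on the control contrast.

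**Effective size.** 882/3 = 294 followed up per arm, and 294/2.7 = 108.9. On the protocol's own terms the effective size is 109 per arm.

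**Power for other contrasts at n = 109.**

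Power = Φ{[(|p2−p1| − c)·√n − 1.96·√(2p̄(1−p̄))] / √(p1(1−p1)+p2(1−p2))}, with c = 0 or, for the continuity correction, c = 1/n.

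Example, 18% v 31%: 0.13·√109 = 1.357; 1.96·√(2·0.245·0.755) = 1.192; √(0.1476+0.2139) = 0.601. Without correction, (1.357−1.192)/0.601 = 0.275, so power is 61%. With correction the first term is (0.13−1/109)·√109 = 1.261, and (1.261−1.192)/0.601 = 0.115, so power is 55%.

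The protocol does not say whether 18% belongs to advice or to counselling. **Both readings are assumptions**, and both are shown.

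| Advice v counselling | Power without / with correction |
|---|---|
| 5% v 18% (the planned contrast) | 86% / 80% |
| 18% v 31% | 61% / 55% |
| 18% v 25% | 24% / 19% |
| 18% v 23% | 15% / 11% |
| 8% v 18% | 59% / 51% |
| 10% v 18% | 40% / 32% |

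**Difference detectable with 80% power**, solving the same formula for p2:

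| Assumed advice rate | Points without / with correction |
|---|---|
| 18% | 16.6 / 17.6 |
| 10% | 14.2 / 15.3 |
| 8% | 13.4 / 14.5 |

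With counselling at 18% and the correction that yields 109, power returns to 80% only if advice is at 5%. That is the leaflet rate, and it would contradict the second hypothesis.

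**Scope of the first hypothesis.** The figures above pool all three departments per intervention. In Table 1 only the SIPS-PAT row uses targeted screening: one department and 131 patients per intervention. Read literally, the first hypothesis compares one department with one department, and an effective size of 109 does not apply to it.

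**Not counted here.** With an intraclass correlation of 0.04 and 131 per cluster, 1 + 130 × 0.04 = 6.2, not 2.7. That is a separate error. It lowers every power figure above, including the planned contrast.

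**The case against.** The strongest reply is that the protocol never claims 80% power for counselling v advice. The 80% is tied to brief intervention v control. The Synopsis sentence argues for a factorial layout and names no pair of arms. Applying 109 to each of three groups is what two comparisons with a common leaflet arm require. No hypothesis is labelled primary, and the second one matches the calculation. This stands in part: the claim is general, and its reach to this contrast is an inference. But nothing limits it to comparisons with the leaflet, and counselling v advice is in the aim, the second objective and the first hypothesis.

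The advice rate is also not in the document, so no single power figure can be called the protocol's own. That stands, and it is why a range is given. The shortfall is present under both readings of the 18%.

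Two stronger readings are tempting. A reader might infer that the arithmetic is wrong; for the contrast it addresses, 109 reproduces exactly. A reader might also infer that the trial plans to treat non-significance as equivalence. The protocol says no such thing, and Planned analysis already commits to odds ratios with confidence intervals.

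**Conclusion.** The concern holds as a mismatch between a general power claim and a calculation for one type of contrast. At the protocol's own effective size of 109 per arm, counselling v advice has 11% to 61% power over the assumed rates tabulated for it. If advice is at 18%, even a second full 13-point gain leaves power at 61%/55%. The detectable difference runs from 13.4 to 17.6 points, depending on an advice rate of 8% to 18% and on the continuity correction.

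These results assume the advice rates shown, the stated factor of 2.7 and pooling over all three departments per arm. Under the targeted-screening wording of the first hypothesis, power is lower still, and that wording has to be reconciled with the second objective and Table 1.

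A reader might go further and say the trial cannot detect any plausible gain from counselling. The documents do not support that, because they give no plausible range for the gain.

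**What to change.** 1. In the Synopsis and the Sample size calculation, limit the power statement to each active arm v leaflet.
2. For counselling v advice, state the power and the detectable difference over a range of advice rates, and label those rates as assumptions.
3. Say whether that contrast uses all nine departments or only those with targeted screening, and align the first hypothesis, the second objective and Table 1.
4. State that a non-significant result for this contrast will not be read as no added benefit. The estimate and confidence interval are already planned.

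The cost is a change of wording and a less favourable stated power. No extra patients are needed. The figures in step 2 should be computed after the design effect has been corrected.

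### The 25% attrition step is wrong (146 per group, not 131), and re-deriving the chain shows that the stated clustering factor of 2.7 does not fit an AED cluster of 131

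*Protocol*

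**What the plan says.** All the inputs stand in the protocol under Sample size calculation.

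- Effect: a "difference between brief intervention and control is of the order 13%, 5% reduction in the control group and 18% in the brief intervention group".
- Error rates: "at the 5% significance level with 80% power, for a 2-sided test".
- Base requirement: "requires 109 patients in each of the 3 groups, a total of 327".
- Attrition: "the potential loss to follow-up across groups is of the order 25" per cent, followed by "Taking this loss into accounts inflates the sample required to 131 in each group, a total of 393 patients per intervention".
- Clustering: the literature and earlier trials "suggest an intra-class correlation coefficient of 0.04 is appropriate", and then "Assuming a cluster size of the order 131 patients this inflates the sample size calculation by a factor of 2.7 requiring patients 393 in each" (that is, per arm). This makes 1179 overall, with at least 882 expected to be followed up at 6 months.

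Elsewhere, 131 is the number per site. The Synopsis says "Each AED will recruit a minimum of 131 patients who are hazardous or harmful drinkers into the trial", and Table 1 under Design shows 131 patients in each of nine AEDs, with three AEDs (393 patients) per intervention.

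**The concern.** Three things in the section do not fit together.

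1. 131 is presented as 109 inflated for 25% loss, and it is not.
2. The figure of 393 per intervention appears before the clustering step and again after it, although a factor of 2.7 is said to lie between the two.
3. The number 131 serves as the individually randomised group size, as the cluster size in the clustering step, and as the recruitment target per AED.

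This section is the only justification of the sample size for the primary outcome. A reader who follows it cannot get from one line to the next, and the mixing of group size with cluster size bears on the design effect and so on the claimed 80% power.

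**Working it through.** **Base number.** Inputs: p1 = 0.05, p2 = 0.18, difference d = 0.13, mean proportion 0.115, two-sided 5%, 80% power.

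- Without continuity correction: n = [1.96 × √(2 × 0.115 × 0.885) + 0.842 × √(0.05 × 0.95 + 0.18 × 0.82)]² / 0.13² = 93.4, so 94.
- With continuity correction: (n/4) × [1 + √(1 + 4/(n × d))]² = 108.2, so 109.

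The plan's 109 is therefore reproduced, and it is the continuity-corrected figure.

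**Attrition step.** Input: 25% loss.

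- Correct: 109/(1 − 0.25) = 145.3, so 146 per group; 3 × 146 = 438.
- Common shortcut: 109 × 1.25 = 136.25, so 137. This does not give 131 either.
- What gives 131: 109 × 1.20 = 130.8. The loss that 131 can absorb is 1 − 109/131 = 16.8%.
- Label: 131 × 3 = 393 is the total over three groups, just as 109 × 3 = 327 is in the sentence on the base requirement.

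**Where the final numbers come from.**

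- From the stated 131: 131 × 2.7 = 353.7, not 393.
- From 109 with 25% loss handled correctly: 109 × 2.7 = 294.3 evaluable; 294.3/0.75 = 392.4, so 393 per arm; 3 × 393 = 1179; 3 × 294 = 882. All three final figures are reproduced.
- Check: 393 × 0.75 = 294.75 evaluable per arm, and 294.75/2.7 = 109.2. At a factor of 2.7 the requirement of 109 is met.

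**Design effect.** Formula: 1 + (m − 1) × ICC, with ICC = 0.04.

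| Cluster size m | Design effect |
|---|---|
| 131 (recruited per AED) | 1 + 130 × 0.04 = 6.2 |
| 98 (131 × 0.75, evaluable per AED) | 1 + 97 × 0.04 = 4.88 |
| 43.5 | 1 + 42.5 × 0.04 = 2.7 |

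The factor 2.7 needs m = 1 + 1.7/0.04 = 43.5. That is close to 131/3 = 43.7, as if 131 had been an arm spread over three AEDs. The protocol does not say so; this is an inference from the arithmetic.

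**Power of the planned 393 per arm (294 evaluable).** Effective size is 294 divided by the design effect.

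| Design effect | Effective n per arm | Power, continuity-corrected | Power, uncorrected |
|---|---|---|---|
| 2.7 (stated) | 108.9 | 80% | 86% |
| 4.88 | 60.2 | 50% | 61% |
| 6.2 | 47.4 | 38% | 51% |

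**Would more patients at the same sites help?** With three AEDs per arm the effective size is 3m/(1 + 0.04(m − 1)). As m grows this approaches 3/0.04 = 75, which is below 109. Larger clusters alone cannot reach the requirement at this ICC.

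**The case against.** The strongest defence is that 131 per group is only an intermediate figure. The number actually planned is 393 per arm, and it equals 109 × 2.7/0.75 with the 25% loss applied correctly. Correcting 131 to 146 and carrying it through the same factor gives 393 to 395 per arm, so recruitment does not change. This stands in full.

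It also disposes of three stronger readings that a reader might take from the faulty sentence:

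- *The plan leaves 98 evaluable patients per group where 109 are needed.* It does not. The 98 is the evaluable number per AED; per arm it is about 294.
- *Power falls to 75% through the attrition slip.* That figure belongs to a trial of 131 per arm randomised individually, which nobody plans.
- *Almost no clustering inflation was applied.* 393/146 = 2.69, so the stated factor was applied.

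For the same reason it would be wrong to keep 131 and annotate it as leaving 98 per group: that would contradict the 882 expected at follow-up.

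One might also defend the wording by noting that 131 per AED times three AEDs is 393 per intervention, as in Table 1. But the sentence starts from 109 in each of three groups and comes before any clustering adjustment, so that meaning is not available there.

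The defence does not cover the design effect. The protocol states a cluster size of about 131 and an ICC of 0.04, and these do not give 2.7.

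**Conclusion.** The attrition step is wrong as written: 146 per group (438 in total), not 131 (393), and the phrase assigning 393 to each intervention is misplaced there. At the stated factor of 2.7, the final 393, 1179 and 882 are sound, and the sample is not short because of this slip.

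The consequence that matters appears when group size and cluster size are kept apart. For the AED clusters actually planned, the design effect is 4.9 to 6.2. Power for 393 per arm is then about 38–50% by the formula behind the 109, or 51–61% without continuity correction, rather than 80%.

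These power figures rest on the protocol's ICC of 0.04, its 5% versus 18% effect and 25% loss, equal cluster sizes, and a normal approximation applied to the effective sample size. They make no allowance for having only three clusters per arm, which would lower power further. The attrition and labelling errors depend on none of the clustering assumptions.

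**What to change.** In the protocol's Sample size calculation:

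1. Replace the attrition result by: 109/0.75 = 146 per group, 438 in total, before clustering. Delete the words that assign the total to each intervention.
2. Stop using 131 for the unclustered group size; keep it for the number recruited per AED.
3. Re-derive the design effect from the actual cluster size (6.2 for 131 recruited, 4.9 for about 98 evaluable), or justify a different ICC and show the calculation.
4. Show how 393 per arm, 1179 and 882 arise, and restate the power for 393 per arm under the re-derived design effect, saying whether continuity correction is used.

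The cost is a wording change and a less favourable stated power. No extra recruitment is asked for.
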